#### Health economics

We will estimate the mean cost of the intervention and other back pain-related NHS services and participants' out of pocket expenses over the three-month study period. We will collect information on the cost of training for the physiotherapists in the DSP group, including the cost of the tutors' time to prepare and deliver the training, the cost of participants' time, travel costs and materials.

Therapy cost will be collected from PCT records. The three-month follow-up questionnaire will include questions about use of medication (prescribed and over-the-counter), GP attendances, inpatient stays, outpatient consultations, and visits to other therapists (NHS and private). Healthcare cost will be estimated using unit costs from the NHS tariff and standard references texts [39].

The 'within-trial' difference in mean costs and the difference in mean quality adjusted life years (QALYs) will be estimated with 95% confidence intervals, allowing for the effects of treatment, baseline pain severity, and treating physiotherapist. These estimates will help us to assess the potential benefits of conducting a definitive trial and economic evaluation. For example, if the DSP is associated with greater healthcare costs and no apparent improvement in health outcomes over this initial three-month period, it is unlikely that further research would be worthwhile, particularly if there is also no clear evidence of a strong patient preference for use of the DSP. However, if cost savings and/or health improvements are observed, it is possible that DSP may be a cost-effective intervention and further research would be warranted.

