#### b. Secondary outcome measures

• Roland Morris Disability Questionnaire (RMDQ) [29] - The most commonly used measure of LBP-related disability in primary care trials.

• Modified Von Korff [30] - A measure of LBP & disability over the preceding month.

• SF-12 [31] - A generic measure of health-related quality of life.

• EuroQol [32] - A generic measure of health utility that is designed for use in RCTs.

• Hospital Anxiety and Depression Scale (HADS) [33] - An established and validated self rating instrument for anxiety and depression.

• Pain Self-Efficacy Questionnaire (PSEQ) [34] - An established measure self-efficacy for people with chronic pain.

• Fear Avoidance Beliefs Questionnaire (FABQ) [35] - The physical sub-scale of FABQ measures attitude to movement in back pain.

• Attendance - we will measure attendance from the physiotherapy department's records.

• Use of health services and costs

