#### Three-month follow-up

For this pilot RCT we will do a single follow-up after three months, when treatment will be complete and maximum benefit from treatment is expected. In addition to measuring satisfaction and repeating baseline measures we will collect data on health service use and health transition [38]. We will send follow-up questionnaires by post, three months after randomisation. We will send postal reminders after two and four weeks, and if necessary, we will collect a minimum data set by phone from non-responders.

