#### Data analysis

Descriptive summary statistics for demographic and baseline data will be provided. The dichotomised responses on the five point Likert scale to the treatment satisfaction question will be analysed by means of a generalised linear mixed model with logit link, fixed effects for intervention and baseline pain severity, and random physiotherapist effects. The estimated intervention effect (odds ratio) will be reported with 95% confidence interval and p-value testing the null hypothesis of no intervention effect. Continuous outcomes will be reported as difference in change from baseline with its 95% confidence interval.

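### The QALY comparison adjusts for baseline pain severity but not for baseline EuroQol utility, which costs precision and leaves the estimate open to chance baseline imbalance

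*Protocol article*

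**What the plan says.** In the protocol article, Health economics states that "the difference in mean quality adjusted life years (QALYs) will be estimated with 95% confidence intervals", and names the terms of the comparison: "allowing for the effects of treatment, baseline pain severity, and treating physiotherapist". The same terms apply to costs.

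Baseline utility is not among them, though the article indicates that it will be available. EuroQol is listed under Secondary outcome measures as "A generic measure of health utility that is designed for use in RCTs". Under Recruitment procedure, a completed baseline questionnaire is a condition of entry. The Three-month follow-up section describes "repeating baseline measures". The article does not itemise the baseline questionnaire, so that EuroQol is in it is a reading of these passages together.

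On timing, "we will do a single follow-up after three months", so there are two utility measurements per patient. On use, "These estimates will help us to assess the potential benefits of conducting a definitive trial and economic evaluation".

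**The concern.** With utility measured only at entry and at three months, the usual QALY is the area under the line joining the two values. Half the weight in that area falls on a value fixed before treatment starts. Between-arm differences in baseline utility therefore enter the outcome by construction, and again through their correlation with three-month utility. Pain severity is related to utility but does not replace it.

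The horizon is a quarter of a year, so even a worthwhile utility gain is a very small number of QALYs. Chance imbalance of ordinary size can be as large. The estimate is one of the inputs to the judgement on a definitive trial, so avoidable noise in it is worth removing.

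**Working it through.** The article gives no utility SD, correlation, expected QALY effect or QALY precision, so there is no figure of the plan's own to reproduce. The number per arm comes from its Sample size section: 150 recruited with 20% loss leaves 150 × 0.8 = 120, or 60 per arm (58 per arm are required).

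**Assumptions.** Utility SD 0.30 at both times. Correlation r = 0.5 between baseline utility (u0) and three-month utility (u3). Pain severity correlated 0.6 with u0 and 0.4 with u3 in size (higher pain, lower utility). QALY = 0.25 × (u0 + u3)/2 = 0.125(u0 + u3). Physiotherapist clustering is ignored.

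**Size of a plausible effect.** A utility gain of 0.05 at three months is worth 0.125 × 0.05 = 0.00625 QALY. Gains of 0.03 and 0.07 are worth 0.00375 and 0.00875.

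**Shift from baseline imbalance.**
- SE of the between-arm difference in u0: 0.30 × √(2/60) = 0.0548.
- No adjustment: 0.125 × (1 + 0.5) × 0.0548 = 0.0103 QALY for a 1-SE imbalance.
- Adjusting for pain: the slope of u0 + u3 on pain is 0.6 + 0.4 = 1.0 (SD units), and a u0 imbalance brings 0.6 of itself in pain. The shift is 0.125 × (1.5 − 1.0 × 0.6) × 0.0548 = 0.0062.
- The same calculation gives 0.0051 at SD 0.25 and 0.0041 at SD 0.20.

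**Standard error of the QALY difference.** The common factor is 0.125 × 0.0548 = 0.00685, multiplied by the square root of the residual variance of u0 + u3 in SD units.

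| Model | Residual variance | SE |
|---|---|---|
| Unadjusted | 2 + 2r = 3 | 0.0119 |
| Pain (as planned) | 3 − 1.0² = 2 | 0.0097 |
| With u0 | 1 − r² = 0.75 | 0.0059 |

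The last row gives no credit for pain. Keeping pain alongside u0 lowers 0.75 to 0.734, and the SE is still 0.0059. The variance reduction against the planned model is 1 − 0.75/2 = 62%. For r = 0.4 it is 1 − 0.84/1.8 = 53%, and for r = 0.6 it is 1 − 0.64/2.2 = 71%.

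**Alternative construction.** If QALYs were computed as gain from baseline, 0.125(u3 − u0), the variance is 2 − 2r = 1. Pain explains (0.6 − 0.4)² = 0.04, leaving 0.96; with u0 it is 0.75. The reduction is 1 − 0.75/0.96 = 22%. A 1-SE imbalance now shifts the pain-adjusted estimate in the opposite direction, by 0.125 × (−0.5 + 0.2 × 0.6) × 0.0548 = −0.0026.

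**Simulation check with other inputs.** With 58 per arm, SD 0.25, r = 0.5, a true effect of 0.00625 and pain–baseline utility correlations of −0.3, −0.5 and −0.7 (correlation with u3 set at 0.7 of these), the SD of the estimate was 0.0098, 0.0090 and 0.0074 under the planned model. With u0 added it was 0.0050 to 0.0052. The chance of an estimate with the wrong sign fell from 27%, 24% and 20% to 10–12%. All models averaged close to the true effect.

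**The case against.** The strongest reply is that the area-under-the-curve formula is nowhere in the article, and an article may leave QALY construction to a fuller document. The Data analysis section also says "Continuous outcomes will be reported as difference in change from baseline with its 95% confidence interval"; it does not name QALYs, but it does not exclude them. This stands as a limit on the size of the point: under gain from baseline the saving is about 22%, not about 62%. It does not remove the point, because adding baseline utility helps under either construction, and the adjustment set is stated in the article and not left open.

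Four stronger readings are tempting, and the documents do not support them.

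- A reader might infer that the estimate is biased. Patients are randomised, so it is unbiased on average, and the reported confidence interval carries the chance-imbalance variance. The harm is lost precision and a shift conditional on the imbalance that occurs.
- A reader might infer that baseline imbalance reaches the QALY estimate undiminished. Pain severity is in the model and absorbs part of it: 0.0103 falls to 0.0062 above, and in the simulations 44% to 90% of the unadjusted carry-over remained.
- A reader might infer that such a shift could settle whether further research is done. The article sets no QALY threshold. Its example of not proceeding combines higher costs, no visible health gain and no clear patient preference, and the Primary outcome section ties progression to satisfaction. Even after the fix, the 95% half-width is 1.96 × 0.0059 = 0.012, about twice the assumed effect.
- A reader might infer that the physiotherapist term is an error, since physiotherapists are nested within arm and a fixed effect would be confounded with treatment. Health economics never says fixed, and Data analysis makes physiotherapist effects random in the primary model with the same terms.

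**Conclusion.** The point holds as a matter of precision and of sensitivity to chance imbalance. The stated QALY model omits a strongly prognostic baseline value that the trial appears to collect and that, under the usual construction, is part of the outcome itself. Under the main assumptions the planned standard error is 0.0097/0.0059 = 1.6 times what it need be (1.5 to 1.9 times in the simulations), and a 1-SE imbalance moves the estimate by about as much as a 0.05 utility gain is worth.

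The SD, the correlations, the plausible gain and the QALY formula are all assumed. A smaller SD or a closer link between pain and utility shrinks the shift. The direction of the precision gain does not change across the values tried. The estimate is secondary and is one input among several, so the change is worth making but nothing else in the plan depends on it.

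**What to change.** In Health economics, give the QALY comparison its own covariate list: fixed effects for intervention, baseline EuroQol utility and baseline pain severity, and a random physiotherapist effect as in the Data analysis section. State the QALY formula in the same sentence. Writing the word random there is a clarification only. The cost comparison can keep its present terms.

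The change costs one covariate in one model. It needs no new data if EuroQol is in the baseline questionnaire, which should be confirmed.

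### Prior health service use appears not to be collected and is not a covariate in the cost comparison, which gives up some precision that a few baseline items could recover

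*Protocol article*

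**What the plan says.** Three places in the protocol article bear on this.

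- **Three-month follow-up.** Service use is set apart from the measures that are repeated from baseline: "In addition to measuring satisfaction and repeating baseline measures we will collect data on health service use and health transition".
- **Health economics, data sources.** The resource-use items sit in the follow-up form: "The three-month follow-up questionnaire will include questions about use of medication (prescribed and over-the-counter), GP attendances, inpatient stays, outpatient consultations", with visits to other therapists also listed. Physiotherapy itself is costed separately: "Therapy cost will be collected from PCT records". The cost of training therapists in the decision support package (DSP) is collected as well.
- **Health economics, analysis.** Differences in mean cost and mean QALYs are to be estimated with 95% confidence intervals, "allowing for the effects of treatment, baseline pain severity, and treating physiotherapist". Pain severity is therefore the only patient-level baseline covariate.

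The secondary outcome list names "Use of health services and costs" without a time point. On the purpose of the economic results, the article says: "These estimates will help us to assess the potential benefits of conducting a definitive trial and economic evaluation".

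**The concern.** Earlier use of medication, GP visits and other therapists is a natural candidate predictor of the same items over the next three months, and pain severity is at best an indirect stand-in for it. The cost model as described leaves out the baseline value of its own outcome. A covariate missing from a model can be added in a later analysis plan, but information never asked for before randomisation cannot be recovered then. That makes it a point for the protocol stage.

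At stake is the width of the interval around the cost difference. The trial is sized for satisfaction, so nothing in the design protects precision on cost. Entry is also mixed: the eligibility section describes referral of patients not back to normal activities after 3-4 weeks, and sooner for those not coping, so prior use may well differ between patients.

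**Working it through.** **1. The plan's own figure.** The article gives no cost SD, target cost difference or correlation. The only figure that can be reproduced is the sample size for satisfaction (Sample size section: 50% against 75%, 80% power, 5% level, taken as two-sided). With pooled variance and no continuity correction:

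n = [1.96 × √(2 × 0.625 × 0.375) + 0.842 × √(0.5 × 0.5 + 0.75 × 0.25)]² / 0.25² = 57.7, so 58 per group, as stated.

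For 20% loss, 58 / 0.8 = 72.5, so 73 per arm or 146 in total, consistent with the stated minimum of 150. With 150 recruited, 150 × 0.8 = 120 are analysed, about 60 per arm.

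**2. Unadjusted precision on cost.** In units of the cost SD, and ignoring therapist effects, the standard error (SE) of the difference is √(2/60) = 0.183.

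**3. Gain from adjusting for prior cost or use.** The SE is multiplied by √(1 − r²), where r is the correlation with three-month cost. This is equivalent to 60/(1 − r²) − 60 extra patients per arm. The values of r are assumptions.

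| r (assumed) | √(1 − r²) | SE reduction | Equivalent extra patients per arm |
|---|---|---|---|
| 0.1 | 0.995 | 0.5% | 0.6 |
| 0.2 | 0.980 | 2.0% | 2.5 |
| 0.3 | 0.954 | 4.6% | 5.9 |
| 0.5 | 0.866 | 13.4% | 20.0 |

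**4. Allowing for pain severity, already in the model.** Let p be the correlation of pain severity with cost, and q its correlation with prior use. Then

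R² = (p² + r² − 2prq) / (1 − q²), and the SE ratio relative to a model with pain severity alone is √[(1 − R²)/(1 − p²)].

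Assume p = 0.2 or 0.3 and q = 0.2 or 0.4.

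- At r = 0.3 the reduction is 2.1% to 3.7%. For the low end (p = 0.3, q = 0.4), R² = (0.09 + 0.09 − 0.072)/0.84 = 0.129 and √(0.871/0.91) = 0.979.
- At r = 0.5 the reduction is 9.9% to 12.2%. For the high end (p = 0.2, q = 0.2), R² = (0.04 + 0.25 − 0.04)/0.96 = 0.260 and √(0.740/0.96) = 0.878.

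Steps 3 and 4 together give about 2-5% at r = 0.3 and 10-13% at r = 0.5.

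**5. Chance imbalance.** With 60 per arm, the between-arm difference in mean prior use has an SE of 0.183 SD. An imbalance of one SE moves the cost difference by r × 0.183: 0.055 cost SD at r = 0.3 and 0.091 at r = 0.5. This movement is part of the unadjusted SE of 0.183 in step 2. It is the same loss seen from another side and should not be counted again.

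**The case against.** The case against is substantial, and most of it stands.

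- **No bias.** A reader might infer that heavy service users falling by chance into one arm would distort the cost result. Patients are randomised, so the difference is unbiased in expectation, and the planned 95% confidence interval already reflects such imbalance. This stands: only precision is lost.
- **Not the deciding quantity.** A reader might infer that the cost difference alone settles whether research continues. The article does not say so. Its example of a reason to stop combines "greater healthcare costs and no apparent improvement in health outcomes over this initial three-month period" and gives weight to patient preference, and the primary outcome section ties the case for a further trial to satisfaction. This stands.
- **Collection at three months only is an inference.** The condensed article does not itemise the baseline questionnaire. The wording of the follow-up section makes the inference strong but not certain.
- **A modest correlation is likely.** Training and study-therapy costs have no baseline counterpart, so prior use can predict only part of total cost. GPs are asked to exclude patients already under secondary care, which removes some heavy prior users. For recent-onset pain, a long look-back would partly precede the episode. This stands and points to the lower rows of the table.
- **No contradiction.** The Data analysis section reports continuous outcomes as change from baseline, and a reader might infer a conflict with costs that have no baseline. The Health economics section gives costs their own analysis, so the text does not establish a conflict.
- **Covariates are often left to an analysis plan.** This answers the modelling half of the point only, since a later plan cannot supply baseline data that were never collected.

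**Conclusion.** The point holds as a cheap gain in precision. It is not an error in the article. As described, the cost difference is adjusted for baseline pain severity and treating physiotherapist but not for prior service use, which appears not to be collected before randomisation. The estimate is unbiased and, on this point, its interval is valid.

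The gain ranges from negligible (0.5-2% of the SE at r = 0.1-0.2) through small (2-5% at 0.3) to moderate (10-13% at 0.5). It rests on an assumed r, assumed correlations with pain severity, about 60 analysed per arm, and an SE that ignores therapist effects. Nothing in the article supports a particular value of r, and the make-up of the total cost makes the lower end plausible.

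**What to change.** Add a few brief resource-use items (medication, GP, outpatient, inpatient, other therapists), covering a stated period before entry, to the baseline questionnaire that patients already return before randomisation. Word them like the follow-up items so that the two can be costed alike. Add baseline cost or use to the cost model, alongside treatment, pain severity and physiotherapist. If these items are already on the baseline form, it is enough to say so and to name the covariate.

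The cost is some respondent burden on a form whose completion is a condition of entry, possible missing values in the new covariate (so say how they will be handled), and a little costing work. No extra patients or visits are needed. If the sponsor judges the burden too great, the present plan remains valid with a somewhat wider interval.
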